##### Effectiveness as a function of language

The generalized linear models for mean change scores will be modified to include a *regimen*-by-*language* interaction term. The analysis strategies will be very similar to those described in the “Analysis plans for objective 1” section—albeit models for mean change scores rather than models for expected proportions.

##### Hypothesis generation/refinement

To enhance understanding of the main overall assessments of effectiveness and to explore the roles of other covariates, we will explore numerous versions of the models for mean change scores. The analysis strategies will be very similar to those described in the “Analysis plans for objective 1” section—albeit models for mean change scores rather than models for expected proportions.

#### Analysis plans for objective 3

We will investigate mediation effects of harsh/neglectful parenting (CTS-PC and PS), parent stress (PSI-SF), and child behavior (ECBI) (*mediators*) on the relationship between PriCARE/*CARIÑO* (*exposure*) and CPS investigations/CPS risk (BCAP) (*outcomes*). Generalized linear model methods similar to those specified for objectives 1 and 2 will be used to investigate direct associations between exposures mediators and mediators outcomes. The exposure-mediator-outcome triplets that demonstrate clinically important magnitudes of effect will be further investigated for mediation. Estimation of the average causal mediation effect, average direct effect, total effect, and proportion mediated and their corresponding 95% CIs will be computed via bootstrap using 500 resamples. In addition, triangulation [94] will be used to contextualize the results of this mediation analysis with the results of the qualitative analysis (described below in the “Analysis plans for objective 4” section) of the intervention’s possible mechanisms of change. These model-building investigations will result in hypothesis generation/refinement.

#### Analysis plans for objective 4

In the last year of the study, clinics will be characterized according to clinician referral, caregiver enrollment, and caregiver attendance rates and 3 high-implementing and 3 low-implementing clinics will be selected for in-depth study. Guided by TDF [78, 79], semi-structured interviews of clinicians, PriCARE/*CARIÑO* facilitators, and caregivers will be conducted at each of the selected clinics. Purposive sampling will be used to capture clinicians with high (top quartile) and low (bottom quartile) referrals and caregivers with high (>3 sessions) and low (≤ 3 sessions) attendance from each clinic. Altogether, we anticipate interviewing 3–5 caregivers per site (18–30 total), 2–3 clinicians per site (12–18 total), and 10 PriCARE/*CARIÑO* facilitators.

Interviews will continue until thematic saturation is reached. Transcribed interviews will be analyzed using qualitative content analysis, a theory-driven approach [95, 96]. This coding approach is both deductive (codes are derived from TDF) and inductive (codes are derived from the data). The goals of the analyses will be to identify barriers and facilitators associated with implementation, to identify targeted implementation strategies that can be evaluated in a future trial, and to identify potential mechanisms of intervention-induced change.

#### Analysis plans for objective 5

The ancillary study will be conducted when 483 enrolled caregiver-child dyads (randomized 1:1) have completed the 6-month follow-up interview. Pre- and post-intervention ECBI scores for 483 enrolled dyads (randomized 1:1) studied during a time of virtual delivery of the PriCARE/*CARIÑO* intervention will be compared to historical scores from 444 dyads (randomized 1:1 or 2:1) previously studied in 3 trials during in-person delivery. As in the case of objective 2, the analyses will rely on a generalized linear model with GEE estimation. The dependent variable will be the ECBI change score computed as the 6-month follow-up score minus the baseline score. Participants lost to follow-up will have missing values. The independent variables will be *treatment regimen* (intervention, control) and *clinical site*. Point estimates with 95% CI estimates will be obtained for the population parameters of interest: total variance, mean change for each regimen, the difference between the two mean changes. The treatment-effect estimates will be presented graphically in forest plot figures. Comparable results will be obtained using the dyad-level data from each of the 3 previous trials. To obtain point and interval estimates of differences among the four studies, the generalized linear model will be expanded to include data from all 4 studies along with use of terms in the regression equation representing *study* and *study*-by-*regimen* interaction. The means and mean differences of interest include those that address regimens, studies, differences between regimens (i.e., treatment effects), and differences between studies. The various study-specific estimates of means, mean differences, and variances will be presented graphically in forest plot figures.

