### Objectives {7}

*The primary objective* is to evaluate the relative effectiveness of PriCARE/*CARIÑO* in reducing the frequency of CPS investigations of suspected CM in the target population of low-income (has Medicaid/CHIP/no insurance), racially diverse, English- and Spanish-speaking families. To better understand the treatment effect, we will also explore potential moderators (measures of caregiver depression, anxiety, and adverse childhood experiences, {ACEs}) of the treatment effects.

*The secondary objective* is to evaluate the relative effectiveness of PriCARE/*CARIÑO* in the target population in terms of the following survey instruments:Reducing CM risk (BCAP)Reducing harsh/neglectful parenting (CTS-PC and PS)Reducing caregiver stress (PSI-SF)Improving child behavior problems (ECBI)Strengthening parent-child interactions (DPICS)

To better understand the treatment effects, we will also explore potential moderators (measures of caregiver depression, anxiety, and ACEs) of the treatment effects.

*The third objective* is to investigate mediation effects of harsh/neglectful parenting (CTS-PC and PS), parent stress (PSI-SF), and child behavior (ECBI) on the relationship between PriCARE/*CARIÑO* exposure and subsequent CPS investigations and CPS risk scores (BCAP). The analyses will be used to generate and refine hypotheses about mediation effects.

*The fourth objective* is to understand barriers and facilitators to PriCARE/*CARIÑO* implementation in pediatric primary care, specifically related to clinician *referral* of eligible dyads, caregiver *enrollment*, and caregiver *attendance* to develop targeted implementation strategies to test in a future trial.

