### Sample size {14}

The study to be conducted in 10–15 clinics will enroll 1932 eligible caregiver-child dyads drawn from the target population of low-income children 2–6 years of age. We anticipate that about 15% of the caregivers will be Spanish speakers. We anticipate that about 200–300 of the 1932 enrolled dyads will experience CPS investigation during the study after 1:1 randomization stratified by clinical site and language. In designing the study and choosing the target sample size, considerations included (1) information from previous studies; (2) the availability of eligible dyads, clinics, and clinic personnel; (3) costs and time requirements; (4) anticipated frequencies of drop-out, missing data values, and nonadherence to protocol; (5) the statistical analysis strategies and methods specified for each of the five objectives; (6) anticipated levels of precision of estimators of key population parameters (estimands); and (7) anticipated levels of power of a hypothesis test procedure concerning the effectiveness of the intervention.

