#### Objective 3 considerations

The investigation of mediation effects will focus on model-building, estimation of effects, and qualitative analysis for purposes of hypothesis generation/refinement. We anticipate that the study design and target sample size will be adequate for these exploratory analyses.

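### Objective 3 reports mediated effects only for triplets whose component effects look large in the same data, so the reported set is size-selected; all eight instrument-level triplets could be reported

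*Protocol article*

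**What the plan says.** The third objective looks at harsh or neglectful parenting (CTS-PC and PS), parent stress (PSI-SF) and child behavior (ECBI) as mediators between the intervention and two outcomes, CPS investigation and the BCAP score.

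Analysis plans for objective 3 sets two steps:
- First, "Generalized linear model methods similar to those specified for objectives 1 and 2 will be used to investigate direct associations" between exposure and mediators and between mediators and outcomes.
- Second, "triplets that demonstrate clinically important magnitudes of effect will be further investigated for mediation". For those triplets the mediated, direct and total effects are estimated, and the "proportion mediated and their corresponding 95% CIs will be computed via bootstrap using 500 resamples".

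The section gives no numeric cut, no split sample, and no statement on whether the bootstrap resamples repeat the screen. The only numeric clinically important difference in the article is the 10-unit ECBI change set for objective 5.

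The status of the aim is clear. Objectives {7} says: "The analyses will be used to generate and refine hypotheses about mediation effects". Objective 3 considerations adds: "We anticipate that the study design and target sample size will be adequate for these exploratory analyses".

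**The concern.** A mediated effect is built from two paths: exposure to mediator (a) and mediator to outcome (b). The plan chooses triplets on the observed size of those same paths, in the same dyads, and then reports the mediated effect only for the chosen ones. An estimate that is seen only when it comes out large is, on average, larger than the truth.

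The bias is uneven. It is negligible for a mediator far above the cut and can be large for one near or below it. Mediators that miss the cut have no mediated effect or interval on record.

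What is at stake is how objective 3 reads. Its product is a set of hypotheses about mechanism, and a later trial would use the reported mediated effects and proportions mediated as starting values. The primary result is not affected.

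**Working it through.** **Can every triplet be fitted?** Four instruments by two outcomes gives 4 × 2 = 8 triplets. Objective 1 considerations requires 20 cases per coefficient: 200/20 = 10 coefficients, which reproduces the article's figure, and 300/20 = 15. Sample size {14} expects that "about 200–300 of the 1932 enrolled dyads will experience CPS investigation". A CPS model with regimen, mediator, language and log follow-up uses 4 coefficients, or 6 with the baseline mediator and a regimen-by-mediator term. Both are within 10. The BCAP models would have about 1932 × 0.90 ≈ 1738 dyads after the 10% loss given in Objective 2 considerations. Model capacity does not require the screen.

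**Inputs for the size of the bias**
- n ≈ 1738, or 869 per arm.
- Design effect in the intervention arm of 1 to 2.2. The upper value is 1 + (9 − 1) × 0.15, from groups of 8–10 (midpoint 9) and ρ up to 0.15. Applied to both arms, 2.2 gives 79.9% power for 20% versus 13% with 966 per arm, against the stated 80%.
- SE(a) = √((DEFF + 1)/869): √(2/869) = 0.048 to √(3.2/869) = 0.061, in SD of the mediator.
- SE(b) for CPS = 1/√(1738·p(1 − p)). With p = 200/1932 = 0.104 it is 0.079; with p = 300/1932 = 0.155 it is 0.066 (log-odds per SD).
- SE(b) for BCAP = 1/√1738 = 0.024 (SD per SD).
- Assumed, because the article gives none: a cut of 0.20 on each path, and the true effects shown below. The errors of a and b are taken as independent and normal.

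**Formula.** For a path with true value θ and cut c, the mean estimate given that it passes is θ + SE·φ(z)/(1 − Φ(z)), with z = (c − θ)/SE. The inflation of a·b is the product of the two conditional means divided by the true product.

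**True paths at the cut (a = b = 0.20).** Here z = 0 and φ(0)/0.5 = 0.798.
- Path a: 0.238 to 0.248, a ratio of 1.19 to 1.24.
- Path b for CPS: 0.253 to 0.263, a ratio of 1.26 to 1.31. Path b for BCAP: 0.219, a ratio of 1.10.
- Mediated effect: CPS 1.51 to 1.63; BCAP 1.30 to 1.36. About 25% of such triplets pass.

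**Other true values, same cut**

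| True a | True b | Outcome | Chance of passing | Mediated effect, reported ÷ true |
|---|---|---|---|---|
| 0.30 | 0.30 | CPS | 85–92% | 1.04–1.08 |
| 0.30 | 0.30 | BCAP | 95–98% | 1.01–1.02 |
| 0.10 | 0.20–0.30 | CPS or BCAP | 1–5% | 2.2–3.0 |
| 0.10 | 0.10 | CPS | under 1% | 5.0–5.4 |

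The ratio is above 1 in every row. The largest ratios belong to triplets that rarely pass.

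**Sensitivity to SE(a).** The objective 2 models use change scores. If the test-retest correlations quoted for the instruments (ECBI 0.75, CTS-PC 0.8) applied here, SE(a) would be multiplied by √(2(1 − r)), giving 0.030 to 0.043. The path-a ratio at the cut becomes 1.12 to 1.17. The mediated effect becomes about 1.12 × 1.26 = 1.41 to 1.17 × 1.31 = 1.53 for CPS, and 1.12 × 1.10 = 1.23 to 1.17 × 1.10 = 1.29 for BCAP. The bias is smaller, with the same direction.

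**The case against.** The strongest reply has five parts.

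- **The aim is exploratory.** The article says so repeatedly and plans triangulation with qualitative interviews. No test, power claim or confirmatory statement rests on objective 3. This stands and sets the severity. It does not make a size-selected set of estimates unbiased.
- **Much of the information is reported anyway.** Objective 2 gives point and interval estimates for every secondary instrument, which covers all four mediators and BCAP. Objective 1 does so for CPS investigation. Exposure-mediator and total effects are therefore public without a screen. This also stands. A reader might infer that a mediator below the cut disappears from view, but its exposure effect does not. Only its mediated effect, direct effect and proportion mediated are absent.
- **The screen alters no estimate.** A reader might infer that it distorts the ranking of mechanisms. It does not: the triplets that pass keep the same estimates and the same order with or without it. The bias lies in which estimates are shown. Reporting all eight would not protect someone who then looks only at the largest.
- **The bootstrap.** A reader might infer that the intervals ignore the screen. The article does not say either way, and such detail is commonly left to the full protocol or analysis plan.
- **Eight is a derived count.** CTS-PC, PS and ECBI have subscales or dimensions, and using them would give more triplets. This stands; eight holds at instrument level only.

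The full protocol or analysis plan might also set a numeric cut. That would make the screen reproducible but would not by itself remove the selection.

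**Conclusion.** The point holds as a minor improvement to an exploratory aim. The article states a rule that makes the reported mediated effects and proportions mediated a size-selected set, biased upward on average for triplets near or below the cut and little biased for those well above it. The direction follows from selecting on the same estimates that form the mediated effect. The size cannot be fixed from the article. The figures of 1.3 to 1.6 times at the cut and 1% to 8% well above it rest on an assumed cut of 0.20 for both paths, independent normal errors and the standard errors shown, and they shrink somewhat if change scores are more precise. The primary and secondary effect estimates are not affected.

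**What to change.** Replace the screening sentence in Analysis plans for objective 3. Estimate and report the mediated, direct and total effects with 95% confidence intervals for all instrument-level triplets: CTS-PC, PS, PSI-SF and ECBI, each with CPS investigation and with BCAP, eight in total. Use clinical importance only to interpret the results, not to decide which are estimated. If subscales are to serve as mediators, list them in advance and report all of them.

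If the screen is kept, state the numeric cuts beforehand and repeat the screen inside each bootstrap resample. This is second best, because triplets below the cut would still have no mediation estimate.

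The cost is a few extra model fits, more if subscales are used, and no new data.

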#### Interim analyses {21b}

Mid-study inspection of the data will not be used to stop the study early and will not be used to change the enrollment sample size. The ancillary study of treatment effects in terms of ECBI change scores has the potential to modify the intervention regimen from virtual delivery to in-person delivery of PriCARE/*CARIÑO*.

### Methods for additional analyses (e.g., subgroup analyses) {21b}

#### Sensitivity analyses objective 1

To guide our level of trust in the main results about effectiveness, sensitivity analyses will be used to evaluate the robustness/fragility of the main results to reasonable perturbations of the assumptions and statistical methods used; for example, examination of the impact of (1) including/excluding questionable data, (2) representing PriCARE exposure in terms of the number of attended PriCARE sessions (dose) instead of intent-to-treat allocation, (3) excluding caregivers assigned to PriCARE who attended ≤ 3 of the 6 sessions, (4) using a generalized logistic mixed-effects model, (5) using a generalized log-linear model for the binary outcome (CPS investigation yes/no) or for the dyad’s number of CPS investigations, (6) using a Cox proportional hazards model for time to first CPS investigation. The sensitivity analyses will only be used to guide our level trust in the main results and guide wording of our conclusion statements.

#### Sensitivity analyses objective 2

To guide our level of trust in the main results about effectiveness, sensitivity analyses will be used to evaluate the robustness/fragility of the main results to reasonable perturbations of the assumptions and statistical methods used; for example, examination of the impact of (1) including/excluding questionable data, (2) using a constrained longitudinal generalized linear model which would be able to include all subjects—even those without follow-up data at 6–8 months, (3) representing PriCARE exposure in terms of the number of attended PriCARE sessions (dose) instead of intent-to-treat allocation, (4) excluding caregivers assigned to PriCARE who attended ≤ 3 of 6 sessions.

### Methods in analysis to handle protocol non-adherence and any statistical methods to handle missing data {20c}

For the main analysis, we will assume that any missing data values were caused by ignorable mechanisms [97]. Additional sensitivity analyses will be used as described in {20b}.

### Plans to give access to the full protocol, participant level-data and statistical code {31c}

This publication grants public access to a concise summary of the full protocol. De-identified individual participant data collected during the trial will be made available beginning 36 months following the article (primary objective) publication and ending 60 months following article publication. Selected code for statistical computations may be available upon request.

## Oversight and monitoring

### Composition of the coordinating center and trial steering committee {5d}

Daily monitoring of the study locally will be done by the research coordinators and the two PIs at their respective institutions. The entire research team will meet at least every other week during subject enrollment.

### Composition of the data monitoring committee, its role and reporting structure {21a}

Study oversight will be under the direction of a Data and Safety Monitoring Board (DSMB) composed of a formal independent board of experts, including investigators with backgrounds in psychology, child welfare research, clinical trials of pediatric behavioral health interventions, and biostatistics.

### Adverse event reporting and harms {22}

The Chair of the DSMB will serve as the safety officer and will be the contact person for serious adverse event reporting. The PIs will be responsible for notifying the DSMB chair and IRB of any serious adverse events when they happen, in accordance with IRB regulations.

### Frequency and plans for auditing trial conduct {23}

Meetings of the DSMB will be held at least two times a year at the call of the Chair. An emergency meeting of the DSMB may be called at any time by the Chair should participant safety questions or other unanticipated problems arise.

### Plans for communicating important protocol amendments to relevant parties (e.g. trial participants, ethical committees) {25}

The date of each amendment, accompanied by a description of the change and the rationale will be submitted to all overseeing safety boards prior to implementing.

### Dissemination plans {31a}

The results of this trial will be published in peer-reviewed journals as well as at national conferences. Results will also be disseminated at the participating health systems through presentations at primary care practitioner-focused conferences, participation in primary care podcast series, and other venues.

## Discussion

In spite of the high prevalence and documented adverse health consequences of CM, there is a paucity of research on preventive interventions [98]. The promotion of clinical research that aims to provide empirical information to support preventive CM interventions was stated as a priority 25 years ago by the National Research Council (NRC), a statement recently reaffirmed by the World Health Organization [99], the NAM, and the NRC [16]. In particular, research on effective CM prevention interventions delivered in primary care settings is lacking. The primary care setting is an ideal venue to engage families in prevention, as it is the only place where most (>95%) US preschool-aged children visit at least once/year [100]. Yet, in 2018, the US Preventive Services Task Force concluded that there was insufficient evidence to assess the balance of benefits and harms of primary care interventions to prevent CM [101, 102]. Thus, there is a critical need for research informing the development and implementation of CM prevention programs in primary care.

In addition to being the largest CM prevention trial with individual randomization, this study addresses three of the key research priorities identified by the NAM and NRC in their report on “New Directions in Child Abuse and Neglect Research.” The first priority is developing and testing new programs for underserved children and families. PriCARE/*CARIÑO* was developed with input from and evaluated in underserved families. The existing evidence base favoring its efficacy is strong [38–41]. Three RCTs and one pre/post pilot have demonstrated improvements in key proximal outcomes, including child behavior problems, harsh parenting, and parent stress scores. Our proposed study is well-designed to evaluate the impact of this promising intervention on CM prevention. Furthermore, our study population is drawn from diverse sites, including clinics in which PriCARE/*CARIÑO* is well established, new sites, academic and private clinics, as well as urban and suburban locations, which will contribute to the generalizability of the results.

The second priority is identifying the most effective ways to implement and sustain evidence-based programs in primary care settings. To achieve the public health impact of reducing CM, PriCARE/*CARIÑO* must not only be effective but must also be widely implemented and sustained [103]. Evidence-based interventions implemented without effective screening, referral, and enrollment processes will make little impact on improving the lives of children and families on a broad scale [103, 104]. This study will generate data critical to conducting a future study of implementation strategies to inform scale-up of parenting interventions in primary care settings. Our study design provides an early opportunity to learn about implementation in diverse practice settings. There is a clear need to understand key PriCARE/*CARIÑO* implementation determinants (barriers and facilitators) and leverage that data to develop strategies to promote the implementation, scale-up, and sustainment of PriCARE/*CARIÑO*.

The third priority our study addresses is the investigation of the longitudinal impacts of CM prevention, which can be challenging and costly to initiate. By including consent for the longitudinal data collection on a cohort of nearly 2000 caregiver-child dyads, this study will lay the foundation for future longitudinal studies of the long-term impact of the program on families. This proposed work will serve as the basis for future longitudinal studies evaluating the continued impact of the intervention on CM rates as well as on additional distal outcomes such as academic performance and mental health diagnoses. Furthermore, by testing multiple proximal outcomes in addition to the more distal outcome of CM and contextualizing the results with qualitative data [105], this study will help to elucidate the mechanisms of change and advance the science of CM prevention.

If successful, results from this study will be used to seek funding from state agencies and payers to sustain PriCARE/*CARIÑO* in primary care, while continuing to refine and study implementation and dissemination strategies, with the ultimate goal of achieving levels of exposure sufficient for breaking the intergenerational transmission of CM.

